**7. Outcome Measures**

***Functional Battery***. *Functional limitations*will be measured with the abbreviated Late-Life Function and Disability Inventory (LL-FDI) (51). *Functional Performance* will be assessed using 3 valid and reliable timed performance-related mobility tasks: 400 meter walk, stair-climb, and lift and carry task (26, 27, 49, 52). Assessments of *Mobility-Related Self-Efficacy* to complete each functional task will also be completed with the tests.

**Anthropometric and Strength Battery.***Muscular strength* will be assessed using standardized one-repetition maximum testing protocols for the chest press and leg extension exercises (24, 53).*Body composition* will be assessed using the Bod Pod (Life Measurement Inc, Concord, CA) whole-body air displacement plethysmography system. The Bod Pod has established validity and reliability as an objective method for estimating body composition (54). Another method study staff will use to measure body composition *and bone density* is the GE Lunar iDXA system, which has been proven to provide excellent precision in measurement of total and regional body composition (in addition to bone density) in obese (68) as well as nonobese adults (69). *Body weight* will also be measured to the nearest 0.1 kilogram using a calibrated and certified balance beam scale.

***QOL Battery.*** Global and disease-specific QOL will be assessed using valid and reliable scales including the Satisfaction with Life Scale (7), the SF-36 (55), and the Functional Assessment of Cancer Treatment-Prostate (56) (FACT-P). Pain and fatigue will also be measured with the short-form McGill Pain Questionnaire (57)and the Brief Fatigue Inventory (BFI) (58).

***Behavioral and Feasibility Measures***. Physical activity will be assessed using the *CHAMPS* (50) and *Leisure-Time Exercise Questionnaires* (59). Objectively determined physical activity will also be recorded using the *LIFECORDER Plus Accelerometer* (Suzuken-Kenz, Inc. Nagoya, Japan). Adherence to the exercise prescription will be monitored using exercise logs, upon which participants will record all exercise performed at the center or independently. Exercise-Related Self-Efficacy will be assessed using valid and reliable Exercise Self-Efficacy, Barrier Self-Efficacy, Multi-dimensional, and Self-Regulatory Self-Efficacy scales (57, 60, 61). Dietary assessments will be obtained using the Fred Hutchinson *Food Frequency Questionnaire* and *Three-day diet records*. All behavioral and self-efficacy assessments have established validity and reliability and have been successfully integrated in [name] and [name] prior research.

*Feasibility Measures***.** Descriptive statistics for assessments of recruitment rates, intervention adherence, adverse events, and retention rates will be calculated prospectively throughout the trial. Feasibility assessments of participants’ satisfaction with the exercise and dietary intervention will also be completed at the end of the 8-week intervention.

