***Objective #2:*** ***To determine the feasibility of delivering an intensive lifestyle exercise and dietary intervention to PC patients undergoing ADT.*** Our*working hypothesis* is that the lifestyle intervention will be a safe, well-tolerated intervention that yields acceptable recruitment, adherence, and retention rates and also yields rates of adverse events that do~~es~~ not differ from a standard of care treatment approach.

***Objective #3: To identify the intermediate variables that account for the beneficial effect of the lifestyle intervention on functional limitations and QOL.*** Our *working hypothesis* is that the beneficial effects of the lifestyle intervention on functional limitations and QOL will be indirect, operating through intermediate disablement process model variables including changes in muscle mass and strength, functional performance, and psychosocial outcomes, such as pain, fatigue symptoms, and self-efficacy.

At the completion of this project, we *expect* to have successfully: 1) determined the feasibility and preliminary efficacy of an intensive lifestyle intervention in PC patients undergoing ADT and 2) identified intermediate variables linking change in exercise and dietary behavior to improvements in select functional and QOL outcomes. The primary *positive impact* of our findings would be that they are the first findings supporting the feasibility and efficacy of an evidence-based lifestyle exercise and dietary intervention for offsetting the adverse effects of ADT in PC patients. Findings from the proposed project will also provide the effect size estimates necessary to inform the design of a subsequent R01 application addressing a definitive randomized controlled lifestyle intervention trial targeting men on ADT. The application is also directly responsive to the goal of encouraging investigators to enter and/or transition into the field of behavioral cancer research.

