**Methods for the Exercise and Diet Intervention Arm (n = 20-25).** The proposed intensive lifestyle intervention, consistent with interventions successfully implemented in prior large-scale lifestyle RCTs (32, 38-41) is a multi-component approach designed to facilitate exercise and dietary behavior change and promote adherence, independent of study staff, to these behavior modifications. The ***exercise component*** involvesacombination of aerobic and resistance exercise. The aerobic stimulus consists of 10-30 minutes of exercise performed at a rating of perceived exertion ranging from 11 (Fairly Light) to 14 (Moderately Hard) on the participant’s choice of a treadmill, stationary cycle, or elliptical trainer. The resistance exercise stimulus involves performing 1-3 sets of 8RM-12RM repetitions at a rating of perceived exertion ranging from 12 (Moderately Hard) to 15 (Hard) of 9 different exercises (leg extension, leg curl, chest press, lat pull-down, overhead press, triceps extension, bicep curl, calf raises, and abdominal curl). Exercise duration and intensity will be gradually increased based on individual exercise tolerance and capacity. All exercise sessions will last 1 hour in duration. ***Behavioral activity counseling***, based upon Social Cognitive Theory (45), is also integrated with exercise to promote adherence to the exercise prescription and participant retention. Counseling is delivered via 8 brief (20-min), small group (3-5 participants) sessions conducted once per week immediately following a center-based exercise session during months 1-2. Participants also receive 4 brief (20-min) individualized activity counseling sessions conducted via biweekly phone calls in months 1-3. *The objective of the counseling is to increase self-efficacy for adoption and maintenance of exercise behavior and facilitate the successful transition from supervised to independent center-based exercise participation during the trial.* The behavioral counseling focuses upon the acquisition and practice of self-regulatory skills in conjunction with a continuous problem-solving model of behavior change to empower participants to exert greater control over their behavior, cognitions, and environment. The behavioral counseling is designed to: a) increase health knowledge of the benefits of exercise and dietary change; b) enhance self-efficacy and positive outcome expectancies through the promotion of a series of successful experiences in changing exercise and eating behavior; and c) improveself-regulation of exercise and eating behaviors. The intervention content includes education and counseling efforts involving goal setting, self-monitoring, stimulus control, cognitive restructuring, and barrier problem-solving strategies. To foster the practice/mastery of the newly acquired exercise and behavioral skills and prevent participants from becoming dependent on the expertise of exercise staff to remain physically active, supervised center-based exercise decreases from 2 sessions/week in weeks 1-6 to 1 supervised sessions/week in weeks 7-8 of the intervention. During weeks 7-8, participants have the goal of completing one center-based exercise session independent of study staff supervision during each week. During month 3, participants will have the goal of completing two center-based exercise sessions independent of study staff supervision. Participants will be provided free access to the center-based exercise facility during all its standard operating hours during weeks 7-12. While the facility is supervised by trained fitness staff members during this time, the participants will have no supervisory contact with the study staff during these independent exercise sessions. The ***advantages of the approach integrating counseling and the titration away from staff supervision***are that it helps participants actively apply their developing exercise and behavioral skills to exercise independently while concomitantly providing them access to the study’s exercise facility to facilitate completion of the independent exercise sessions during Weeks 7-12, which also allows us to evaluate uptake of independent exercise adherence in months 2-8. The efficacy of this approach for promoting exercise and dietary behavior change has been demonstrated in prior RCTs on which [name] has served as principal and co-investigator (38-41).

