
- *Self-monitoring*: develop awareness and commitment to tracking/recording of desired exercise and dietary behaviors
- *Goal-setting*: Setting short and long-term, process and outcome-related goals for target exercise and dietary behaviors
- *Stimulus Control*: Development of appropriate behavioral, environmental, and reinforcement strategies that help to facilitate adoption and maintenance of change in exercise and dietary habits (e.g., appropriate exercise pacing, providing oneself with exercise and dietary reminders, identifying appropriate rewards for reaching desired exercise and dietary goals, developing healthier grocery shopping/cooking strategies)
- *Barrier problem-solving*: Use of a social problem-solving approach to identify, practice, and implement self and peer-initiated strategies for overcoming common barriers to exercise and dietary behavior.
- *Cognitive restructuring*: Develop a more positive orientation towards exercise and healthy eating (e.g., monitoring affect during exercise to optimize affect/enjoyment, motivational interviewing to identify positive motives and attitudes for changing exercise and dietary behavior).

**Methods for the Standard of Care Intervention Arm (n = 20-25).** Men randomized to the standard of care arm will receive usual PC treatment as well as educational literature describing the American Institute of Cancer Research dietary and physical activity guidelines. To equate contact between treatment arms to levels consistent with similar, contemporary lifestyle intervention trials (32, 38), 20-min phone contacts delivered by [name] clinic staff focusing on routine aspects of PC self-management will be conducted biweekly with men in the standard of care arm. As an incentive to promote retention across the trial, men randomized to standard of care will also receive 2 supervised exercise training sessions and dietary counseling sessions following the completion of the 3 month assessment. Men will complete assessments of all outcomes scheduled at baseline and months 2, and 3.

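### Exercise adherence is taken from participants' own logs, although every session prescribed in weeks 1-12 is held at a staffed centre where attendance could be recorded

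*Protocol*

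**What the plan says.** Section 7 (Behavioral and Feasibility Measures) names the data source: "Adherence to the exercise prescription will be monitored using exercise logs, upon which participants will record all exercise performed at the center or independently". The text available mentions no attendance register, staff record or check-in.

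The same section makes adherence a feasibility result: "Descriptive statistics for assessments of recruitment rates, intervention adherence, adverse events, and retention rates will be calculated prospectively throughout the trial". Objective #2 in section 3 hypothesises an intervention that "yields acceptable recruitment, adherence, and retention rates".

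Section 6.5 (Exercise and Diet Intervention Arm) sets the sessions:
- Supervised: "supervised center-based exercise decreases from 2 sessions/week in weeks 1-6 to 1 supervised sessions/week in weeks 7-8 of the intervention".
- Weeks 7-8, in addition: "participants have the goal of completing one center-based exercise session independent of study staff supervision during each week".
- Month 3: "During month 3, participants will have the goal of completing two center-based exercise sessions independent of study staff supervision".

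On the independent phase, section 6.5 adds: "While the facility is supervised by trained fitness staff members during this time, the participants will have no supervisory contact with the study staff". It also says that the move away from supervision lets the team evaluate independent adherence in months 2 to 8, while free access to the centre covers weeks 7-12.

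Self-monitoring is the first topic in the counselling outline. Its aim is to "develop awareness and commitment to tracking/recording of desired exercise and dietary behaviors".

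The appendix schedule for the lifestyle arm does not repeat the month 3 goal of two sessions. It leaves the month 3 frequency to the participant.

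**The concern.** The men know their assignment and are coached to exercise and to record it. Their own entries are then the only named evidence of whether they did so. Because recording is itself a taught skill, the log is part of the intervention as well as its measurement.

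This matters most in the independent phase. No study staff are present, and the protocol wants to learn whether exercise continues without them. A better source is close at hand, since these sessions also take place at the centre with fitness staff on duty.

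At stake is how far the adherence figure that informs the feasibility conclusion, and the planning of a definitive trial, can be trusted.

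**Working it through.** The protocol states no adherence rate, threshold or denominator, so there is no figure to reproduce. The check counts the sessions and then asks how far self-report could move the rate.

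**Sessions prescribed in weeks 1-12 (section 6.5)**
- Supervised: 6 weeks x 2 + 2 weeks x 1 = 14.
- Independent, weeks 7-8: 2 x 1 = 2.
- Independent, month 3: the unit is not stated. Two per week gives 4 x 2 = 8; two in total gives 2.
- Total: 14 + 10 = 24, with 10/24 = 42% independent; or 14 + 4 = 18, with 4/18 = 22% independent.

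**Over-reporting confined to independent sessions**

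Let *t* be true independent attendance and *f* the share of missed independent sessions logged as done. Supervised attendance is set at 80% and taken as correctly logged. The values 80%, *t* = 40-60% and *f* = 10-50% are assumptions.

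True rate = (14 x 0.80 + n_ind x t) / N

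Reported rate = true rate + (n_ind / N) x f x (1 - t)

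| N (n_ind) | t | True | Reported, f = 10% | Reported, f = 50% | Excess, points |
| --- | --- | --- | --- | --- | --- |
| 24 (10) | 40% | 15.2/24 = 63.3% | 65.8% | 75.8% | 2.5 to 12.5 |
| 24 (10) | 60% | 17.2/24 = 71.7% | 73.3% | 80.0% | 1.7 to 8.3 |
| 18 (4) | 40% | 12.8/18 = 71.1% | 72.4% | 77.8% | 1.3 to 6.7 |
| 18 (4) | 60% | 13.6/18 = 75.6% | 76.4% | 80.0% | 0.9 to 4.4 |

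Rounded, the excess is about 2-13 points over 24 sessions and 1-7 points over 18.

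**Ceiling**

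If true attendance is 80% throughout and every missed independent session is logged as done, the reported rate is (11.2 + 10)/24 = 88% or (11.2 + 4)/18 = 84%.

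**Denominator**

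Take a man who attends all 14 supervised sessions, both independent sessions in weeks 7-8 and two sessions in month 3. He scores 18/24 = 75% on one reading of the month 3 goal and 18/18 = 100% on the other.

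**Unreturned logs (conditional)**

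Sections 6.1 and 8 both allow for 20% attrition. Assume 80% adherence among men who return logs and 0-50% among the 20% who do not. The rate over all men is 0.8 x 0.80 + 0.2 x 0 = 64% up to 0.8 x 0.80 + 0.2 x 0.50 = 74%. The gap from 80% arises only if men who leave are dropped from the denominator, and the protocol does not say that they are.

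**The case against.** Several counter-arguments carry weight.

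- **The log form is not shown.** The contents page lists exercise logs among the appendix forms, but the form itself is not in the text available. A staff signature on it cannot be ruled out. This stands, so the claim is only that no other source is named. Section 7 still says that participants do the recording.
- **Most sessions are observed.** A reader might infer that over-reporting runs through all sessions and could bring the reported rate close to 100%. The documents do not support this, because study staff are present at 14 of the 18 or 24 sessions. With an even 80% true attendance the ceiling is 88% or 84%.
- **Losing logs need not inflate the rate.** A reader might infer that the rate rests only on men who keep returning logs. The protocol is silent on unreturned logs, section 8 states the intention-to-treat principle, and a counting rule could sit in an analysis plan that is not shown. If a missing entry counts as a session not done, log loss lowers the rate. Retention is also reported separately.
- **Nothing hinges on a threshold.** A reader might infer that adherence decides whether the programme goes forward. No such rule is stated: feasibility measures are descriptive, and section 8 gives the primary aim as estimating effect sizes.
- **Other activity measures exist.** The accelerometer and questionnaires give context. However, the accelerometer is worn for 7 days at assessments and the questionnaires are self-report, so neither checks individual sessions.
- **Attendance is not the whole prescription.** Being present does not show minutes, sets or exertion, and centre records cannot cover exercise elsewhere or months 4-8. Nor does the protocol say that the facility keeps entry records by person. All of this stands. It is why attendance should be reported beside the logs and should not replace them.

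**Conclusion.** The point holds as a modest, cheap improvement. The choice of data source is made in the protocol's own outcome section, and a less biased source is available, or probably available, for every session prescribed in weeks 1-12. The weakness lies in the 4-10 independent centre sessions. Under the assumed rates, self-report there overstates overall adherence by about 2-13 points over 24 sessions or 1-7 points over 18. The protocol supplies neither attendance nor misreporting rates, so these ranges show scale and are not predictions.

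The 64-74% figures for unreturned logs illustrate a counting rule that the protocol does not state, and they are not part of the finding. The point concerns exercise adherence only; diet is assessed separately. Adherence informs the feasibility conclusion and does not trigger a stated decision.

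The unclear month 3 goal is a separate textual problem in the same measure, because it changes the denominator from 18 to 24.

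**What to change.** Add one paragraph to section 7:
- Make session attendance in weeks 1-12 a co-reported adherence measure, in all men randomised to the lifestyle arm.
- Take it from a study-staff register for the 14 supervised sessions and, for the independent centre sessions, from facility sign-in or check-in where available.
- Keep the logs for session content (minutes, sets, exertion), for exercise elsewhere and for months 4-8.
- Report log-based adherence beside the attendance rate, and show sessions that are logged but not verified as a separate count. Scoring them all as missed would bias the rate downward.

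Reconcile the month 3 goal in section 6.5 with the appendix schedule, which leaves that frequency to the participant, and state the unit of the goal. Which reading applies is for the investigators to settle.

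The cost is a sign-in sheet or, if the facility keeps one, an entry record. Study staff already attend the supervised sessions. The reported rate may come out somewhat lower.

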**12. References**

**APPENDIX**

**Study Schedule for Diet and Exercise Intervention Group**

|  |  | | **Month 1** | | | | **Month 2** | | | | **Month 3** | | | | **Months 6-8** |
| --- | --- | --- | --- | --- | --- | --- | --- | --- | --- | --- | --- | --- | --- | --- | --- |
|  | **Oncology**  **Clinic**  **Visit** | **Baseline**  **and Randomization** | **Week**  **1** | **Week**  **2** | **Week**  **3** | **Week**  **4** | **Week**  **5** | **Week**  **6** | **Week**  **7** | **Week**  **8** | **Week**  **9** | **Week**  **10** | **Week**  **11** | **Week**  **12** | **Weeks 24-32** |
| **Sign Consent** | **x** |  |  |  |  |  |  |  |  |  |  |  |  |  |  |
| **iDXA Scan** | **x** |  |  |  |  |  |  |  |  |  |  |  |  | **x** |  |
| **Physical Assessment**  **(*functional and strength battery, anthropometric measures)*** |  | **x** |  |  |  |  |  |  |  | **x** |  |  |  | **x** | **x** |
| **Supervised Exercise Sessions** |  |  | **2x** | **2x** | **2x** | **2x** | **2x** | **2x** | **x** | **x** | Frequency determined by participant | | | |  |
| **Behavioral Counseling** |  |  | **x** | **x** | **x** | **x** | **x** | **x** | **x** | **x** |  |  |  |  |  |
| **Behavioral Follow up by telephone** |  |  |  | **x** |  | **x** |  | **x** |  | **x** |  | **x** |  | **x** |  |
| **Nutrition Counseling** |  |  | **x** | **x** | **x** | **x** | **x** | **x** | **x** | **x** |  |  |  |  |  |
| **Nutrition follow up by telephone** |  |  |  |  |  |  |  |  |  |  | **x** |  | **x** |  |  |
| **Quality of Life Questionnaires** |  | **x** |  |  |  |  |  |  |  | **x** |  |  |  | **x** | **x** |
| **Behavioral & Feasibility Questionnaires** |  | **x** |  |  |  |  |  |  |  | **x** |  |  |  | **x** | **x** |
| **National Institutes of Health FFQ and Fruit & Vegetable Screener** |  | **x** |  |  |  |  |  |  |  |  |  |  |  | **x** | **x** |
| **Three Day Diet Records** |  | **x** |  |  |  |  |  |  |  |  |  |  |  | **x** | **x** |

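### Objective 2 compares adverse-event rates between arms with no common way to elicit non-serious events, while contact in weeks 1-12 is 22 (or 20) occasions against 6

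*Protocol*

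**What the plan says.** Section 3, Objective #2, expects the lifestyle intervention to show "acceptable recruitment, adherence, and retention rates and also yields rates of adverse events" that do "not differ from a standard of care treatment approach". That is a statement about a difference between arms.

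The only plan for these data is in section 7, Feasibility Measures: "Descriptive statistics for assessments of recruitment rates, intervention adherence, adverse events, and retention rates will be calculated prospectively throughout the trial". Section 8 repeats it in substance. Section 9 adds CTCAE 3.0 grading of the events that have been reported and immediate reporting of serious events. No section describes how non-serious events are elicited, and neither Appendix schedule has a row for adverse events.

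On contact with intervention men, section 6.5 says that "supervised center-based exercise decreases from 2 sessions/week in weeks 1-6 to 1 supervised sessions/week in weeks 7-8 of the intervention". It adds: "Participants also receive 4 brief (20-min) individualized activity counseling sessions conducted via biweekly phone calls in months 1-3". The Appendix row "Behavioral Follow up by telephone" shows six such calls instead, in weeks 2, 4, 6, 8, 10 and 12. Two nutrition calls follow in month 3.

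For control men, section 6.5 provides that calls by "clinic staff focusing on routine aspects of PC self-management will be conducted biweekly with men in the standard of care arm". The Appendix shows six, in the same even weeks. Both arms attend the same assessments at weeks 8, 12 and 24-32.

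**The concern.** A recorded event rate is the product of how often events occur and how often someone hears of them. Here the second factor differs by arm in frequency, setting, staff and topic. Exercise staff see intervention men in person. Control men speak by telephone with clinic staff about prostate cancer self-management. Section 6.5 says the control calls are meant to bring contact into line with similar trials, but the schedule does not equalise the chance that an event is heard.

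The events most exposed are minor and short-lived, such as aches and strains, which an exercise programme could plausibly cause. If true rates are equal, the intervention may look less safe than it is. If there is a real excess, its size cannot be separated from detection. How events are collected is a protocol matter, and an analysis plan cannot recover events that were never asked about in control men.

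**Working it through.** The protocol states no adverse-event rate, margin or power, so there is no figure of its own to reproduce. The check counts contacts and then asks what they imply.

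**Contacts in weeks 1-12, outside assessment visits**

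| | Intervention, Appendix | Intervention, section 6.5 | Control |
|---|---|---|---|
| Supervised sessions | 2 x 6 + 1 x 2 = 14 | 14 | 0 |
| Behavioural calls | 6 | 4 | 0 |
| Nutrition calls | 2 | 2 | 0 |
| Control-arm calls | 0 | 0 | 6 |
| Total | 22 | 20 | 6 |
| Ratio to control | 22/6 = 3.7 | 20/6 = 3.3 | |

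Group and nutrition counselling held straight after an exercise session is not counted as a separate occasion. Adding the two shared assessments (weeks 8 and 12) to the Appendix counts gives 24 against 8.

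**Weeks with at least one contact**

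- Intervention, Appendix: weeks 1-8 (sessions), 9 and 11 (nutrition calls), 10 and 12 (behavioural calls), so 12 of 12.
- Intervention, section 6.5, if its 4 calls all fall in weeks 2-8: weeks 1-9 and 11, so 10 of 12.
- Control: 6 of 12.

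**Effect on recorded rates when true risks are equal**

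Assumptions, none of them from the documents: events arise evenly over 12 weeks; each stays reportable for D weeks; each contact that falls in that window records it with probability q, the same in both arms; intervention contact is counted once per week (weeks 1, 2, ..., 12) and control contact every second week (weeks 2, 4, ..., 12).

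- D of 1 week or less: a weekly contact falls in the window with probability D and a two-weekly one with probability D/2. The ratio is qD / (qD/2) = 2.0 for any q. With contact in 10 of 12 weeks it is 10/6 = 1.67.
- D = 2: control men have one contact in the window, so detection is q. Intervention men have two, or one if the event starts in the last week, so detection is (11 x [1 - (1 - q)^2] + q)/12. At q = 0.3 this is (11 x 0.51 + 0.30)/12 = 0.49 against 0.30, ratio 1.64. At q = 0.5 it is (11 x 0.75 + 0.50)/12 = 0.73 against 0.50, ratio 1.46. At q = 1 the ratio is 1.0.
- D = 4, by the same reasoning: 1.46, 1.24 and 1.0 at q = 0.3, 0.5 and 1.

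Parity therefore needs both a reportable period of at least two weeks and full recording at every contact.

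**Scale in this trial**

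Take a true risk of 30% in both arms (assumption), D = 1 and q = 1. The recorded rates would be 30% and 15%. With 16 men per arm (20 less 20% attrition) to 25 per arm, a two-sided 5% test has power of only 0.17 to 0.24 for that contrast. The comparison is too small to help tell a detection effect from a real difference.

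**The case against.** The strongest reply is that the protocol is silent on elicitation, not wrong about it. Section 9 is a summary of the monitoring plan, and an event form may exist elsewhere. Several parts of this reply stand.

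- A reader might infer that the plan simply counts events as they come up. The protocol does not say so. The sentence in section 7 says when summaries are computed, not how events are found.
- A reader might infer that control men have nothing but a biweekly call. They attend the same week 8, 12 and 24-32 assessments. Both schedules include behavioural and feasibility questionnaires at those visits, though their content is not itemised. Pain and fatigue scales are also given to both arms at those times, which covers aches in part, although a symptom score is not an event count.
- A reader might infer that recorded rates will double, or that the whole adverse-event comparison cannot be interpreted. Neither follows. The ratio of 2.0 depends on assumed duration and recall and on the Appendix call count. Serious events are reported by one route in both arms, and lasting events are much less affected if each contact asks fully.
- A reader might infer that a distorted event rate passes into the next trial. The protocol carries forward effect sizes and path coefficients and does not mention an adverse-event rate.
- With equal true rates the distortion counts against the intervention, so it gives no false reassurance. The summaries are descriptive, in a pilot whose stated primary aim is estimating effect sizes.

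What the reply does not remove is that the protocol names a between-arm comparison, builds unequal contact into the design, and states nothing that would make detection equal.

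**Conclusion.** The point holds for minor, short-lived, non-serious events. With 22 (or 20) contacts against 6, and no common method of asking, such events can be recorded more often in the intervention arm when true rates are equal. The apparent ratio runs from 1.0 to about 2.0, with about 1.7 as the upper figure if the 4 calls of section 6.5 all fall in weeks 2-8. These values rest on assumed event durations and recall, on equal recording probability per contact in both arms, and on a simplified contact pattern. They show that rates can differ through detection; they do not estimate a bias. The efficacy estimates are untouched. The safety part of Objective 2 is affected enough to justify a change before data are collected, because missed control-arm events cannot be restored later.

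**What to change.** State in section 7 that the between-arm comparison of non-serious adverse events uses only events elicited with one identical checklist and one recall period, at contacts both arms share:

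- the assessment visits at weeks 8, 12 and 24-32;
- the biweekly calls common to both arms, once the number of behavioural calls (4 in section 6.5, 6 in the Appendix) has been reconciled.

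Show the week 24-32 count apart from weeks 1-12, because section 6.5 gives control men supervised exercise and dietary sessions after the month 3 assessment. List events noted at exercise sessions or nutrition calls separately for the intervention arm, outside the comparison. Leave serious-event reporting as in section 9.

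The cost is a one-page checklist and a few minutes at contacts already scheduled. The compared count will omit events volunteered only at sessions, but these are still listed and reported.
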